## Abstract

**Background:**

Type 2 diabetes mellitus (T2DM) is one of the leading noncommunicable diseases that require diabetes self-management (DSM) practices. This study proposes to develop a customized mobile health (mHealth) app integrated with a hospital information system (HIS) to enable real-time, two-way transfer of information between the patient and physician. The captured information in the electronic health record will facilitate physicians to have a chronological account of the patient’s diabetes history and enable tweaking of the treatment.

**Objective:**

The objectives of the study are (1) to develop the HIS-integrated Electronic Diabetes Diary (EDDy) per the end-user expectations at a tertiary care hospital in a south Indian state with a high prevalence of T2DM and (2) to evaluate and test adherence to EDDy in the management of T2DM.

**Methods:**

The study will be carried out in 3 phases. Phase 1 involved in-depth interviews with primary end users to gather information regarding their expectations from the hospital-based EDDy. Phase 2 will use this information to develop a customized mHealth app using an iterative model of software development. Phase 3 will involve a pre- and posttest design; the developed app will be tested among consenting patients, where physicians will receive the patients’ data through the HIS-integrated mHealth app. The pre- and posttest values will be analyzed for adherence leading to improvement in patients’ self-management of blood glucose, user experience, glycemic control, and clinical utility.

**Results:**

Phase 1 was completed on November 28, 2023. Phase 2 commenced in December 2023 and will end in May 2025. Phase 3 will follow afterward.

**Conclusions:**

The proposed app will include a convenient and simple alert system that enables the patient to test glucose values at self-selected intervals, provide grading options to enter diabetic-related complications, enhance patients’ knowledge of tracking and managing the complications of diabetes, and help in maintaining the visual representation of glucose values and complications. The simplicity and usability of the modules are its novelty, which may motivate the patients to keep track of their glucose values and help them attain better health outcomes.

**Trial Registration:**

Clinical Trial Registry India CTRI/2023/03/051077; http://tinyurl.com/4tau4ndb

**International Registered Report Identifier (IRRID):**

PRR1-10.2196/50732

## Introduction

In India, 11.8% of the population have diabetes per the National Diabetes and Diabetic Retinopathy Survey released by the Ministry of Health and Family Welfare in 2019, and this is projected to have a steady rise of 3.8% annually [1]. This prevalence is higher in the southern states and union territories of India [2]. *The Indian Glucose Monitoring Device Market Reports of 2020* [3] suggested that the use of glucometer was always on the rise, and it was specifically noticed that there was an exponential increase in its sale during the COVID-19 pandemic period. Technology-enabled self-management has been increasingly recommended, along with proper medication and lifestyle modification, to tackle diabetes. There are numerous diabetes managements apps available in the Google Play store; however, subscription to such apps is not proportional to the population with diabetes [4]. Literature from other parts of the world suggest that the adoption of digital diabetes-monitoring solutions is expected to reach 21% by 2027 [5].

Diabetes is an irreversible chronic condition that need to be well managed by altering lifestyles, food habits, and physical activities [6]. However, a standard diabetes management regimen may not be feasible to everyone around the globe, as each of these factors varies according to geographical locations and general living conditions [5]. Using customized information that is specific to the local lifestyle may be more effective and easier to ensure adherence. Existing literature suggests that nonadherence to treatment regimen and irregularity in following a diabetes-friendly lifestyle leads to poorly managed diabetes and poor disease outcomes [7]. To enhance the existing measures to manage T2DM, efficient methods needs to be formulated to ensure adherence to treatment regimen [8]. The success of such activities requires active involvement of the patients and caregivers. They should be motivated to follow T2DM management instructions from health care professionals.

This study setting already has an existing system of manual diabetes information documentation that expects its patients to record their self-management of blood glucose (SMBG) practices systematically and submit them to the treating physician during consultation. These glucose monitoring records are used by the physician to evaluate the patient’s glycemic status and make appropriate clinical decisions. This study proposes to automate this process and make it more efficient for the patients and physicians. The proposed electronic diary is expected to reduce the loss of documented values, minimize errors, as well as motivate the patients to effectively make use of technology and manage their condition.

A pilot study was conducted to analyze the knowledge and attitude to digital diabetes management practices among 50 existing patients with diabetes, which indicated that ignorance and technological illiteracy are the main reasons behind nonuse of digital apps among them. Those who used digital apps, such as mobile health (mHealth) apps, suggested that the information available is more general in nature and that they find it difficult to navigate and comprehend the information, eventually leading to the discontinuation of its use.

## Methods

### Overview

The study will be carried out in the outpatient department (OPD) of the endocrinology department at a tertiary care hospital in a south Indian state, and it is divided into 3 phases. In phase 1, a qualitative study was conducted; in phase 2, the mobile app with be developed and integrated with a health information system (HIS); and finally, in phase 3, the developed app will be tested for its feasibility using a pre- and posttest design.

The study is based on the principles of the “theory of change,” where stakeholders will be consulted through in-depth interviews (IDIs) to identify the deterrents to acceptance and adherence of electronic diabetes-monitoring practices, potential challenges, as well as ethical issues related to electronic information sharing. This feedback will provide the cues for the development of a customized electronic diabetes-monitoring system. The study would also attempt to identify the reasons that would lead to the discontinuation of electronic monitoring practices among patient with T2DM and address them by developing a more user-friendly mHealth app. This study will also analyze the patient acceptance of the mHealth app and their adherence to SMBG practices.

The model will then be developed and integrated with an HIS. Finally, it will be tested among patients with T2DM regarding their acceptance and adherence to using the Electronic Diabetes Diary (EDDy), its usability, contextual relevance according to user expectation, and clinical utility in terms of glycemic control.

### Ethical Considerations

This study has been approved by the Institutional Ethics Committee (IEC; IEC No:223/2022). The participants personal information will be anonymized, and all privacy, confidentiality, and compensation policies will be adhered to as per the IEC guidelines.

### Pilot Study

As a precursor to this study, a pilot study was conducted in a tertiary care hospital among 50 patients with T2DM to understand the existing personal record-keeping practices, the challenges they face, and their awareness of personal record keeping. The perception, expectations, and concerns of the target population were studied using a validated questionnaire survey. Patients with T2DM who are within the age group of 40-65 years were included in the study. The study setting encouraged patients with T2DM to document their SMBG values by providing a data sheet to enter the values and asking patients to bring it with them when they come for a doctor’s appointment. It is a valuable tool for the doctor to assess the values and make better clinical decisions in the management of the disease.

A cross-sectional study was conducted, and a purposive sampling technique was followed to select the participants. A mixed-type questionnaire (both open- and close-ended questions) was used to collect data.

### Phase 1

#### Study Design

IDIs with key stakeholders was carried out to identify the reasons for nonadherence, expectations from EDDy, and mandatory requirements to develop the intervention mechanism. The key stakeholders included the following participants:

Patients with T2DMTheir caregiversTreating doctorsDiabetes counselors (includes nursing counselors, diet counsellors, and physiotherapists)

#### Sample Selection

The IDI participants were enrolled according to the following criteria: patients who own an Android smartphone and those who regularly attend doctor’s appointments (ie, those who visit the OPD at least once in the last 6 months). Patients who are literate, can understand the local language (Kannada or Tulu) or English, aged 40-65 years, and have hemoglobin A_1c_ values between 7% and 10% were selected to ensure homogeneity. Patients with gestational diabetes and other terminal illnesses were excluded. The IDIs were conducted among the immediate caregivers of the patients (ie, those who are actively involved in the care of the patient). To understand the practical aspects of the treatment and management of patients, physicians, nurses, and counsellors were also interviewed.

Even with the availability of various diabetes management apps, studies suggest they are not very popular among the general population. The reason for this underuse and nonadherence, along with their expectations from mHealth apps, are the key areas that were addressed among patients with T2DM and their caregivers. The doctors and diabetes counselors were interviewed to understand the challenges they face while managing patients with T2DM and their SMBG practices.

#### IDI Process

The IDIs focused on the perspectives of patients with T2DM and their caregivers along with physicians and diabetes counselors who are actively involved in the care of patient with T2DM. Additionally, IT and health information management professionals were also consulted on ethical challenges and technical expertise. The IDI guide was designed based on the objectives of the study and the content was validated by experts. The IDI process is shown in Figure 1.

Qualitative data generated during the IDIs will be analyzed by using ATLAS.ti software (version 8; ATLAS.ti), and a report will be prepared. Based on the report, the researchers and the subject experts will identify the most feasible options that will be considered for incorporation into EDDy.

**Figure 1 figure1:**
[figure not shown]
Process of the in-depth interviews (IDIs). IEC: Institutional Ethical Committee; IRC: Institutional Research Committee; KH: Kasturba Hospital.

### Phase 2

#### Development of EDDy

Phase 2 is the main part of this research, where the software will be developed based on inputs from the IDIs and the literature. The mobile app will be developed on Android Studio (Google) using an iterative model design.

The iterative model (Figure 2) is one of the Software Development Life Cycle models, where the development of a system goes through repeated cycles (iterative) and is conducted in smaller portions at a time (incremental) [9]. As and when the different modules of the app are developed, they will be tested and reviewed against the end user’s expectation, and accordingly, modifications and further development will be done. This process will enable easier debugging and fixing of errors as and when tested.

**Figure 2 figure2:**
[figure not shown]
Iterative model of Software Development Life Cycle. EDDy: Electronic Diabetes Diary; HIS: hospital information system.

The development and testing of the app will involve development, pilot-testing, and debugging at each phase. Each iteration will be subjected to the development, testing implementation, and analysis of each component of EDDy. The components for incorporation into the software will be validated by the following experts:

An endocrinologistQualitative expertsThe IT team at the hospital

The expected pattern and time period for phase 2 are as follows.

#### System Development

##### Step 1: Requirements

This is the phase where the stakeholders’ requirements are enquired and compiled, which was primarily covered in phase 1. The captured data will be systematically entered into Microsoft Excel for further evaluation.

##### Step 2: Analysis

The compiled information will be divided into feasible and nonfeasible items as per the system development and HIS-interfacing requirements. This step will be conducted with the researchers and technical experts.

##### Step 3: Designing and Development

This step will be done by a software developer with the support of a researcher. Once the feasible requirements are sorted and finalized by the researcher, the design of the app will take place. First, a prototype of the system will be developed, and the requirements for each module of the app will be determined. This step includes the coding of the app based on the design. Android Studio, an open-source program for Android software development, will be used to develop the proposed mobile app. The iteration process has 3 phases, where a patient module and a physician module will be designed, and integration with an HIS will be performed as depicted in Figure 2.

##### Step 4: Implementation

After development, each module of EDDy will be pilot-tested for its intended use. The modules will be connected to a web-based backend database application to help the validation of content, visualization, and analysis of the data collected.

##### Step 5: Testing and Quality Assurance

The developed app will undergo a standard testing and quality assurance process to identify and rectify any issues and bugs. Each module will be validated during testing to ensure its intended performance.

##### Step 6: Analysis of Feedback

A pilot test among 2 potential users will be carried out at each level of iteration, and user experience will be measured using a Likert scale on various aspects of the app’s functionality. The parameters that will be measured during the piloting process will be the app’s functionality, usability, accessibility, compatibility, and performance under real-life scenarios.

Once the app is fully developed and interfaced with an HIS, it will be installed in the respective systems of the stakeholders and tested for its performance. Gaps and technical glitches will be rectified at each phase.

##### Step 7: Deployment

The final app will be deployed among end users (patients and physicians).

##### Step 8: Maintenance

The final app will be integrated into an HIS. Once the module is fully functional, the study will proceed to phase 3.

#### Expected Outcomes From EDDy

The app is expected to improve the SMBG practices in patients with T2DM. EDDy is expected to motivate the use of the app (*acceptability*) and improve the user experience on the *contextual relevance*. The *ease* of using the customized system and a clinician’s feedback mechanism through the physician module is expected to improve the *clinical utility* of the app. It is expected that adherence to using the app would improve compliance to treatment protocol, thus improving treatment outcomes.

The entry of information into EDDy can be done either by the patient or their caregiver. The entry of SMBG values by the patient is a standard clinical practice in patient management. The current practice is that these self-monitored blood glucose values (SMBG data) is maintained by the patient on a printed form provided by the hospital. It is standard practice that such SMBG data function as a mechanism that helps physicians to optimize medication in routine clinical practice [10].

A researcher will provide instruction to the patient or patient party on how data entry needs to be done on the app. Additionally, a built-in user manual will be provided with the system. This will be developed as a part of the app development. A multilingual *user manual* or *instructional videos* will be developed to assist the patient in using EDDy. The pictogram in Figure 3 represents the workflow of EDDy.

**Figure 3 figure3:**
[figure not shown]
Prototype of EDDy.

### Phase 3

#### Study Design

Phase 3 will involve testing the adherence and usability of the developed app. This phase will use a pre- and posttest design among 48 patients with diabetes selected through purposive sampling.

At a 5% level of significance with 80% power and an effect size of 0.25, the minimum sample size required for a single-group, repeated measures study design involving 1 primary quantitative outcome (adherence) measured across 3 time points (preintervention, after 3 months, and after 6 months; correlation among repeated measures is 0.3) to understand the adherence to EDDy integrated with an HIS is 38 individuals. Incorporating a dropout rate of 20%, the minimum sample size requirement is 48 individuals.

The sample size was computed using G*Power (version 3.1.9; Universität Düsseldorf). The sample size may be amended (if required) based on pilot study findings.

The study setting will be the endocrinology OPD of a tertiary care hospital in coastal Karnataka, India.

Regarding study participants, patients with T2DM who have regular follow-up records will be considered for the study.

This study will analyze the adherence of patients with T2DM to EDDy in comparison to the existing manual method of documentation. Adherence will be evaluated in terms of the following:

Adherence of entering SMBG values as predetermined by the patient: The study participants will be instructed to fix the frequency that they will monitor their blood glucose; based on this frequency, they will be prompted to conduct the glucometer testing and enter the values into EDDy. The values will be stored in the app and will be transferred to the server on a regular basis as the EDDy is integrated with an HIS.Adherence to diabetes self-management (DSM) practices: Pre- and posttest adherence to DSM practices will be analyzed using the same content-validated questionnaire.Adherence to routine blood investigations and screening regimen: Pre- and posttest adherence to periodic blood investigation and comorbidity screening will be analyzed.

The inclusion and exclusion criteria for sample collection will remain same as that of phase 1.

Phase 3 will be evaluated in 3 intervals:

First evaluation (preintervention): During enrollment into the study, the patients will undergo an entry survey using a content-validated questionnaire to analyze the current DSM and SMBG practices they follow.Second evaluation (follow-up): An interim follow-up will be conducted in the third month.Third evaluation (postintervention): The same questionnaire used in the first evaluation will be used to evaluate DSM and SMBG practices after the intervention.

The study participants will be provided with EDDy on their mobile phones and will be trained to use it along with standard diabetes care. Training materials will be a part of the app for patient’s ready reference. The pre- and posttest process is shown in Figure 4.

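### Phase 3 uses purposive sampling and leaves contributors to the app eligible, so adherence and usability levels may reflect who was selected

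*Protocol article*

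**What the plan says.** The Protocol article, Phase 3, Study Design, fixes the way patients are chosen: "This phase will use a pre- and posttest design among 48 patients with diabetes selected through purposive sampling". The same section treats the phase as a powered quantitative study, a "single-group, repeated measures study design involving 1 primary quantitative outcome (adherence) measured across 3 time points", and ends its sample size statement with "Incorporating a dropout rate of 20%, the minimum sample size requirement is 48 individuals".

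On eligibility it says: "The inclusion and exclusion criteria for sample collection will remain same as that of phase 1". It adds that patients with a record of regular follow-up will be considered. The phase 1 criteria (Phase 1, Sample Selection) require an Android phone, regular attendance, literacy in a stated language, age 40 to 65 years and HbA1c of 7% to 10%. The only exclusions named there are gestational diabetes and terminal illness.

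The place is a single clinic: "The study setting will be the endocrinology OPD of a tertiary care hospital in coastal Karnataka, India". The Overview in Methods sets the whole study in one endocrinology outpatient department. Phase 2 (Development of EDDy) builds the software from the phase 1 interviews and the literature.

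**The concern.** Purposive selection suits the phase 1 interviews, where the aim is to gather informative views. Phase 3 has a different aim: to measure how well patients adhere to the app, accept it and find it usable. Purposive selection leaves room to choose patients on traits that bear directly on those outcomes, such as comfort with technology or existing diary habits. The article gives no selection purpose or rule that would close that room. With no control group, levels of adherence and user ratings are read straight from whoever was enrolled.

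A second route is prior involvement. Patients interviewed in phase 1 remain eligible, and phase 2 testers are not excluded. Phase 3 (Analysis) defines contextual relevance as how well the content meets the expectations that users voiced in phase 1. A former interviewee would in part be rating whether their own requests were met.

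At stake is what the adherence, acceptance and usability results describe: the eligible patients of this clinic, or a subset whose selection cannot be characterised.

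**Working it through.** **1. The plan's own sample size.** Inputs from Phase 3, Study Design: "At a 5% level of significance with 80% power and an effect size of 0.25"; three time points; "correlation among repeated measures is 0.3"; one group. Assumptions: the effect size is Cohen's f (the convention of the software named) and sphericity holds (epsilon = 1), since the article states neither.

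Formula for a one-group repeated measures F test, with n patients and m = 3 time points: λ = n·m·f²/(1 − ρ), df1 = m − 1, df2 = (n − 1)(m − 1).

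| n | λ | df1, df2 | Power |
|---|---|---|---|
| 37 | 37 × 3 × 0.0625/0.7 = 9.91 | 2, 72 | 0.794 |
| 38 | 38 × 3 × 0.0625/0.7 = 10.18 | 2, 74 | 0.806 |

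The smallest n with at least 80% power is 38. Dropout: 38/(1 − 0.20) = 47.5, rounded up to 48. Both stated figures reproduce. The sampling method is not an input, so this point implies no different n.

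**2. Who can enter.** Set side by side, the sections give this chain:
- Phase 1 interviewees met the phase 1 criteria.
- Phase 3 applies the same criteria.
- No listed exclusion concerns earlier participation.
- The interviews feed the app, and phase 3 judges the app against expectations voiced in phase 1.

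The number of patients interviewed is not given. For phase 2, Step 3 describes three iteration phases and Step 6 has two potential users test at each level. If all testers differ (assumption), that is 3 × 2 = 6 people, and 6/48 = 12.5% of the sample if all were patients and all enrolled. Some may be physicians, so the share could be lower.

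**3. Direction of the effect.** For levels measured after the app is introduced (use, ease, acceptance), choosing engaged patients pushes results up. For pre/post change it can work the other way. On a measure bounded at 100, a group starting at b can gain at most 100 − b, so each point that selection adds to the baseline removes a point of possible gain.

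**4. Scale, on assumed figures only.** The article gives no adherence rate and plans no interval for a proportion, so this is purely illustrative. Take 38 evaluable patients, true adherence p of 50% to 70%, and a selection shift s, so that q = p + s and SE = √(q(1 − q)/38). Coverage of a nominal 95% interval for the eligible clinic population is Φ(1.96 − s/SE) − Φ(−1.96 − s/SE).

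| Shift s | Coverage, over p = 50% to 70% |
|---|---|
| 0 points | 95% (half-width about 15 to 16 points) |
| 5 points | about 89% to 91% |
| 10 points | about 66% to 76% |
| 15 points | about 26% to 51% |

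Enrolling more patients in the same way would not remove such a shift.

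**The case against.** The strongest reply is that phase 3 is a single-group feasibility test, where non-probability samples are common, and that purposive may mean no more than enrolling consenting patients who meet the criteria. The article does not say who selects or on what trait, and it gives homogeneity as the reason for some criteria. It also condenses a fuller protocol, which may hold the recruitment procedure, a screening log and a rule on earlier participation; the figure showing the pre/post process is not available. Nor does it say that earlier participants will enter. This stands as far as it goes: the absence of a log from the article is not itself a fault. But the sampling method is stated, the carry-over of the criteria is stated, and a better method is available in the same clinic.

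Three stronger readings are tempting, and the article supports none of them:
- *Results will be biased upward.* The basis of selection is not described, and step 3 shows that the pre/post change could be reduced instead.
- *The power calculation is undermined.* It is a model-based calculation of within-person change, it reproduces, and it does not depend on how patients are sampled. The article states no confidence interval or precision target. Consecutive enrolment is also non-probability sampling; its gain is less discretion over who enters.
- *The pilot allows the bias to be sized.* In the pilot, 22 of 50 patients (44%) documented their values. That sample was itself purposive, and documenting values at all is not adherence to the app, so it is no unbiased benchmark.

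**Conclusion.** The point holds as a design weakness that is cheap to correct. Purposive selection, with contributors to the app still eligible, leaves room for selection related to the outcome. It risks optimistic levels of adherence and usability, a baseline ceiling that could hide improvement, and a partly circular rating of contextual relevance for former interviewees. It also weakens any extension to all patients with type 2 diabetes, which the Discussion (Expected Findings) looks towards.

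The size of the bias cannot be derived from the article, and the coverage figures above rest wholly on assumed rates and shifts. The planned 38 evaluable and 48 enrolled patients stand. The conclusion assumes that the fuller protocol does not already restrict selection or exclude earlier participants.

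**What to change.** In Phase 3, Study Design:
- Replace purposive sampling with consecutive enrolment of eligible, consenting patients attending the endocrinology outpatient clinic until 48 are enrolled.
- Keep a log of patients screened, declined and enrolled, with age, sex, HbA1c and current documentation habit, so that selection can be judged.
- Exclude phase 1 interviewees and phase 2 pilot testers. If that is not practicable, flag them and report contextual relevance and usability without them as well.
- Limit conclusions to the enrolled clinic population.

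The cost is a change of wording and a simple log, with the same number of patients. Recruitment may be slightly slower, and observed adherence may be lower. By the stated timeline phase 3 starts only after phase 2 ends, so the change can be made before enrolment.

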#### Analysis

Study participants will be followed up for 6 months and will be analyzed primarily for their adherence to using EDDy. It will be assessed based on patients’ willingness to use it, the ease of use, their acceptance of EDDy in terms of the contextual relevance, and the clinical utility. The participants will undergo an exit survey at the end of the study period using a validated questionnaire. It will be specific for assessing the qualitative parameters such as *user experience*, *glycemic control*, *adherence leading to improvement in their SMBG*, and *clinical utility.*

The qualitative outcomes are as follows:

Ease of use and adherence: User’s perception on accessing the various modules in the app, ease of entering information, ease for retrieving information, and ease of comprehending informationGlycemic control: Adherence in terms of regular monitoring and tracking of blood glucose values to keeps it under check, leading to well-managed T2DMContextual relevance: Relevance of the contents of EDDy in terms of the user expectations and requirements as expressed in phase 1 of the studyAdherence to SMBG and DSM practices: Reminders and alerts that ensure adherence to medications, insulin injections, regular glucose testing, and comorbidity screeningClinical utility: Improvement in treatment outcomes due to adherence to reminders or alerts and monitoring of blood glucose, adherence to medication, and follow-ups

The frequency will be tested based on the Diabetes Co-Conditions Screening Checklist provided by the Association of Diabetes Care & Education Specialists [11].

The following standard tools will be used for assessment, which are modified according to the study requirements and will be content validated by experts:

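### Phase 3 has a single group and no pre-app value for logging in EDDy, so it cannot support the stated comparison with manual recording or the crediting of gains to reminders

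*Protocol article*

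**What the plan says.** The Phase 3 Study Design section describes a pre- and posttest study of 48 purposively sampled patients. Its sample size statement gives "the minimum sample size required for a single-group, repeated measures study design involving 1 primary quantitative outcome (adherence) measured across 3 time points", the time points being "preintervention, after 3 months, and after 6 months; correlation among repeated measures is 0.3", and concludes that the number needed "to understand the adherence to EDDy integrated with an HIS is 38 individuals".

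The same section states the comparative aim: "This study will analyze the adherence of patients with T2DM to EDDy in comparison to the existing manual method of documentation". It then lists three adherence components: entry of glucose values into EDDy at a frequency the patient fixes and the app prompts; diabetes self-management (DSM) practices, by the same questionnaire before and after; and blood investigations and comorbidity screening, before and after. The entry and final evaluations use one questionnaire covering both DSM and SMBG practices.

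The Analysis section makes adherence to using EDDy the primary focus. Among its outcomes it defines clinical utility as "Improvement in treatment outcomes due to adherence to reminders or alerts and monitoring of blood glucose", a list that goes on to medication adherence and follow-ups.

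No concurrent manual group, crossover or run-in on the paper form is described.

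**The concern.** Two conclusions are announced that one group observed before and after cannot supply: that adherence to EDDy differs from adherence to manual recording, and that outcome gains are attributable to reminders and the behaviours they prompt.

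The first has a further difficulty. The component most specific to EDDy has nothing to be compared with, because before the app there is no prompt, no EDDy entry and no stated patient-fixed frequency. The sample size nevertheless treats adherence to EDDy as one quantitative outcome with a preintervention value.

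If the plan is followed as written, a rise in reported self-management could be published as an advantage of EDDy over paper, or as an effect of its reminders, when the data show only that patients changed while enrolled.

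**Working it through.** **1. The plan's own figure.** Inputs from Phase 3 Study Design: alpha 0.05, power 0.80, effect size f = 0.25, m = 3 time points, correlation 0.3, one group. The G*Power formula for a within-subject factor, with sphericity assumed, is

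lambda = f² × n × m / (1 − rho), with df1 = m − 1 and df2 = (n − 1)(m − 1).

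- n = 38: lambda = 0.0625 × 38 × 3 / 0.7 = 10.18, df 2 and 74, power 0.806.
- n = 37: lambda = 0.0625 × 37 × 3 / 0.7 = 9.91, df 2 and 72, power 0.794.

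The minimum is therefore 38. With 20% dropout, 38 / 0.80 = 47.5, rounded up to 48. Both figures reproduce.

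**2. What that test answers.** It tests whether the mean of one outcome is equal across three time points in one group. It has no term for manual recording as an alternative to EDDy and none for reminders.

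**3. Which components have a preintervention value.**

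| Adherence component | Before the app | After the app |
|---|---|---|
| Glucose values entered into EDDy at the set frequency | None possible; no manual counterpart stated | App log |
| DSM and SMBG practices | Entry questionnaire | Same questionnaire |
| Investigations and screening | Pretest assessment | Posttest assessment |

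The first row cannot fill the first of the three time points assumed in step 1. The second and third rows can be compared before and after.

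**4. What else changes between the two measurements.** By the plan's own account (Phase 2, Expected Outcomes From EDDy; Phase 3, Study Design), patients receive researcher instruction, training material and physician feedback together with the app, alongside standard care, over 6 months. All of these act on everyone at the same time as the reminders. With no unexposed group, the change in rows two and three is the sum of them all.

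**5. A consequence for the remedy.** The 38 rests on three comparable measurements. If the chosen outcome were measured only at entry and 6 months, with f = 0.25 and correlation 0.3 kept as assumptions, then m = 2. At n = 38, lambda = 0.0625 × 38 × 2 / 0.7 = 6.79, df 1 and 37, power 0.718. Reaching 80% would take 46 evaluable patients, or 46 / 0.80 = 57.5, rounded up to 58 enrolled. The article mentions a third-month follow-up without saying which instruments are used then. That detail may sit in the full protocol and is not a fault here, but the remedy depends on it.

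**The case against.** The strongest reply is that this is openly a single-group study. The Methods overview describes phase 3 as testing feasibility, the sample size matches the design, and clinical utility appears in a list of qualitative outcomes assessed by questionnaire and physician interview, not as a planned causal estimate. That stands as far as it goes: the design is a legitimate choice, and the sample size is not in error. It does not rescue the comparative and causal wording, which a feasibility study does not need.

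A reader might infer that the plan has no like-for-like measure at all, or that it will set recalled baseline practice against app logs. The document does not support this. The same questionnaire covers DSM and SMBG practices at entry and end, screening is assessed before and after, and nothing says survey answers will be compared with log counts. The gap is confined to EDDy entry.

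A reader might also infer that the HbA1c window of 7% to 10% produces spurious improvement, since "The inclusion and exclusion criteria for sample collection will remain same as that of phase 1". This does not hold as an argument here. The window is bounded on both sides, so regression to the mean could be downward, nil or upward depending on a clinic mean the document does not give. No HbA1c endpoint is named, and the primary outcome is adherence. Nor does the pilot finding that 28 of 50 patients kept no record show how far questionnaire and log would disagree.

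**Conclusion.** The point stands. Phase 3 can show within-patient change in questionnaire-reported practices and in investigations and screening, and can describe use of EDDy after it is provided. It cannot show that EDDy does better than manual recording, or that gains come from reminders.

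One of three adherence components lacks a preintervention value, and it is the one closest to the stated primary interest. The other two are sound as before-after measures but uncontrolled. The 38 and 48 are correct for a within-group test over three time points.

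The document does not establish that a control arm must be added. That would be a different study, and its size would turn on a between-group effect that the document does not give. This verdict rests on the published text alone. It would soften if the full protocol defined a preintervention counterpart for EDDy entry, but the lack of a control would remain.

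**What to change.** 1. Base the pre-post adherence comparison, and the primary adherence outcome, only on measures obtained identically at each time point: the same questionnaire, including SMBG documentation, and investigations and screening counted over equal windows. Apply them at month 3 as well, so that the basis for 38 evaluable patients holds.
2. Report EDDy log entries against the patient-set frequency descriptively, as adherence after the app is provided.
3. As an optional supportive analysis, count earlier SMBG records of any kind, printed form or personal diary, over an equal window where they are available. Treat absent records as missing, not as zero. In the pilot 21 of 50 patients used a personal diary, so scoring a missing form as zero would class diary keepers as non-documenters and favour EDDy. The Introduction says of the existing records that "These glucose monitoring records are used by the physician to evaluate the patient", but nothing says the hospital keeps them, so completeness is unknown.
4. Replace the comparative sentence in Study Design and the causal phrase in the clinical utility definition with within-patient change from baseline. State that no causal effect of EDDy or its reminders versus manual recording will be concluded.

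Cost: mainly wording, and the same questionnaire at month 3 if that is not already planned. No extra patients are needed if three comparable measurements are kept. The claims become more modest. Phase 3 had not begun when the article was written, so the change can be made before any of its data exist.
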